**Figure 2 f2:**
[figure not shown]
Example of focal dose escalation.

**Table 3 T3:** Dose constraints.

Structures and dose constraints (acceptable deviations)			
**Rectum**	V20Gy ≤ 50% (optimal) V28Gy ≤ 15% (20%) V32Gy ≤ 10% (15%) V35Gy ≤ 2 cc (4 cc) V38Gy ≤ 1 cc Dmax ≤ 40.6 Gy	**Bladder**	V20Gy ≤ 50% (optimal) V28Gy ≤ 15% (20%) V32Gy ≤ 10% (15%) V38Gy ≤ 6 cc V39.5Gy ≤ 2 cc
**Rectum_PRV**	Dmax ≤ 45 Gy	**Bladder_PRV**	Dmax ≤ 46 Gy (optimal)
**Urethra_PRV**	Dmax ≤ 52 Gy D10% ≤ 47.2 Gy D50% ≤ 42 Gy (optimal)	**Penile Bulb**	V20Gy ≤ 40% (90%) V35Gy ≤ 4%
**Bowel_Small**	V25Gy ≤ 20 cc (40cc) V30Gy ≤ 2 cc Dmax ≤ 3 5Gy	**Bowel_Large**	V25Gy ≤ 20 cc (40 cc) Dmax ≤ 38 Gy
**Femur_R and Femur_L**	V28Gy ≤ 5%		

The primary endpoints of the trial will be 6-week and 6-month gastrointestinal (GI) and GU toxicity using the Common Terminology Criteria for Adverse Events version 5.0 (CTCAE v5.0). While other prospective trials have confirmed the safety of an mpMRI-defined intra-prostatic boost with external beam radiotherapy (4, 6), the proposed boost volume in ARGOS/CLIMBER will be based on mpMRI and PSMA PET-targeted PET (17), and thus there is a need to demonstrate the safety of such a multi-modality defined boost volume. Secondary endpoints include Quality of life measured by the Expanded Prostate Cancer Index Composite (EPIC-26) questionnaires and 5-year disease-free survival (DFS) as a composite of BF, patient death, or development of clinical metastases or institution of salvage ADT.

All grade 3 or higher toxicity will be reported to the principal investigator. An independent data and safety monitoring board (IDSMB) will perform a formal interim analysis for safety and toxicity when half of the patients have been accrued or after 1 year, whichever comes first. The study will be discontinued if the projected rate of grade 3 or higher urinary or bowel toxicity exceeds 30%. IDSMB will meet at least annually to review trial data.

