Unique to the ARGOS/CLIMBER protocol is the integration of longitudinal imaging with PSMA-directed PET and mpMRI pretreatment and posttreatment. Serial PSMA PET/MR images will be collected at baseline, 6 months, and 2 years to characterize the imaging response of prostate cancer to treatment and potentially identify imaging biomarkers (including pharmacokinetics, radiomics, and quantitative PET and mpMRI metrics) that predict for 5-year DFS (**Table 4**). Additionally, baseline collection of diagnostic tissue biopsy samples and serial collection of blood and urine over multiple time points (baseline, 6 months, 1 year, and 2 years post-SBRT) will be performed for correlative biologic biomarker analyses with imaging changes, DFS, and toxicity posttreatment. Analysis of prostate biopsy at baseline and 2 years will allow for correlation of histopathology with PSMA PET/MR images. We will investigate whether a negative posttreatment PSMA PET/MRI is correlated with a negative 2-year posttreatment biopsy and long-term disease control (36, 39). We also plan to examine novel clinical prognostic biomarkers (i.e., absolute percentage of Gleason Pattern 4 on biopsy and 4-year PSA response rate) and their correlation with imaging findings and 5-year DFS.

**Table 4 T4:** Schedule of events.

Event	Weeks (week 0 is start of RT)										Q6mo (30–60mo)
	−3	−2	0	1 EOT	3	8 (6 weeks post-RT)	6 months post-RT	12 months post-RT	18 months post-RT	24 months post-RT	
	V1	V2	V3	V4	V5	V6	V7	V8	V9	V10	V11–15
Start alpha antagonists, simethicone	x										
Fiducial marker insertion		x									
Simulation and planning		x									
Treatment (5 fractions q2d, 10–12 days)			x	x							
CTCAE v5.0	x		x	x	x	x	x	x	x	x	x
EPIC-26 questionnaires	x		x	x		x	x	x	x	x	x
PSA and testosterone	x					x	x	x	x	x	
PSMA PET/MRI		x					x			x	
Liquid biomarker collection		x				x	x	x		x	
Transperineal biopsy		x								x	

CTCAE v5.0, Common Terminology Criteria for Adverse Events version 5.0; PSA, prostate-specific antigen; PSMA, prostate-specific membrane antigen.

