For PET/MRI, a whole-body MRI scout scan (to plan the study) and B0 homogenization using gradient enhancement (HUGE) acquisition (to correct for truncation of arms) will be acquired first. In both acquisitions, the table moves continuously for approximately 1 min as it scans the subject from head to thigh. Whole-body PET/MRI is acquired in multiple bed positions. For men of average height, 5 overlapping table positions will be used, with taller subjects requiring an additional table position. At each table position, a 5-min PET acquisition will be acquired along with simultaneous MRI consisting of MRI-based attenuation correction, coronal T2-weighted fast spin-echo with Short-TI Inversion Recovery (STIR) sequence during flat breathing, and axial Half-Fourier Acquisition Single-shot Turbo spin-Echo (HASTE) single-shot T2-weighted sequence. For thoracic and abdominal table positions, the HASTE MRI will be captured over 4 breath-holds of 14 s. If unable to do so, these can be done with flat breathing only.

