#### Disease-Free Survival

Five-year DFS will be determined as a composite of biochemical control, patient death or development of clinical metastases, or institution of salvage ADT. DFS will be estimated with a Kaplan–Meier (KM) curve, with the 5-year estimate extracted from the KM curve.

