#### Translational Imaging Endpoints

Changes in SUV metrics (SUVmax, SUVmean) within PSMA PET regions of interest (ROI) will be compared between the pre-RT PSMA PET and the 6-month post-RT PSMA PET. ROIs to be examined will include the dominant intra-prostatic lesions (DILs), the prostate as a whole, and, in the cases of men with PET-detected nodal disease, involved node ROIs. Descriptive statistics and diagrams (i.e., waterfall plots) will be used to characterize changes in SUV metrics. A linear mixed model with random intercept by an individual to account for the correlation present within individuals will be used to compare pretreatment vs. posttreatment SUV values at multiple timepoints. Overall response rates will be calculated in accordance with recent consensus guidelines (46).

Intra-prostatic mpMRI (T2W, DWI, and DCE-MRI) acquired pre-RT and 6 and 24 months post-RT will be reported by expert readers based on PI-RADS 2.1 and the complementary Prostate Imaging for Recurrence Reporting (PI-RR) system to identify intra-prostatic ROIs (44). Quantitative MRI metrics will be extracted, including ADC and pharmacokinetics parameters derived from dynamic PET and DCE-MRI. Radiomics approaches will be used to characterize the evolution of higher-level feature changes in PET and mpMRI over the course of treatment.

We will correlate changes in PET and mpMRI metrics at 6 and 24 months with 5-year DFS using linear regression models. We will also perform supervised machine learning to train support vector machines and random forest classifiers to predict response based on the pretreatment images. We will also perform a delta-radiomics analysis to predict response based on the radiomics trajectory computed from the first two time points. We will measure the performance of the classifiers using a cross-validation design, with metrics including the area under the receiver operating characteristic (ROC) curve and the error rate, false-positive rate, and false-negative rate computed at a point on the ROC curve that best balance the false-positive and false-negative rates. We will develop radiomics-based classifiers to predict 5-year DFS.

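### The 6- and 24-month study scans can prompt events that count in 5-year DFS, so the planned imaging-DFS correlation is open to incorporation bias

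*Protocol article*

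**What the plan says.** The Study Design section of the protocol article defines 5-year DFS "as a composite of BF, patient death, or development of clinical metastases or institution of salvage ADT", and the Disease-Free Survival section repeats the composite. Neither place ties clinical metastases to an imaging method or states what leads to salvage ADT.

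On timing, Study Design says: "Serial PSMA PET/MR images will be collected at baseline, 6 months, and 2 years". Table 4 shows the same visits. On coverage, PET Imaging Acquisition says: "Whole-body PET/MRI is acquired in multiple bed positions". The post-treatment mpMRI "will be reported by expert readers based on PI-RADS 2.1 and the complementary Prostate Imaging for Recurrence Reporting (PI-RR) system".

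The stated aim is to "potentially identify imaging biomarkers" that predict 5-year DFS. Translational Imaging Endpoints sets the analysis: "We will correlate changes in PET and mpMRI metrics at 6 and 24 months with 5-year DFS using linear regression models". It adds radiomics classifiers for 5-year DFS and a delta-radiomics analysis that uses the first two scans. The regions of interest for the PET metrics are the dominant intra-prostatic lesions, the whole prostate and, in men with PET-detected nodal disease, the involved nodes.

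**The concern.** When a test is judged against an outcome that the test itself can help to declare, the association is partly built in. Two of the four DFS components, metastases and salvage ADT, depend on a clinician finding or acting on something, and a study scan at 6 or 24 months is an obvious source. If a suspicious scan leads to salvage ADT, the man becomes a DFS event and his scan counts as a correct prediction. The same holds if the scan was a false positive, a risk that the article's own background raises for PSMA PET after earlier treatment.

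What is at stake is the translational claim that imaging change predicts 5-year DFS. The primary toxicity endpoint, the sample size and the Kaplan-Meier estimate of DFS are not touched.

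**Working it through.** **Does the text allow the overlap?**

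- Outcome: metastases and salvage ADT count as events, with no modality or trigger given (Study Design; Disease-Free Survival).
- Predictor: change on scans at 6 and 24 months, both earlier than 60 months (Study Design; Table 4).
- Reach of the scan: whole body for PET/MRI, so nodal and distant disease can be seen.
- Separation: the article mentions no withholding of post-treatment reads, no event review blind to them, and no rule for events found on a study scan.

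The overlap is therefore possible as written. Its strength differs by metric:

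- Involved-node regions: direct, since the measured region may itself be what is acted on.
- Any region, when salvage ADT is started on a scan finding: direct.
- Intra-prostatic regions and a new distant metastasis: weak, since the metastasis lies outside the measured region.
- Delta-radiomics: shares the problem through the 6-month scan. Classifiers built only on pretreatment images are affected less directly.

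**Figures in the document.** The article gives no DFS event rate and no precision for the imaging-DFS analysis. Its only design figure is the toxicity power of 81%, which reproduces: Φ[(0.15 − 1.645 × √(0.30 × 0.70/50)) / √(0.15 × 0.85/50)] = Φ(0.0434/0.0505) = 0.805. It has no bearing on this point.

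**Illustration of size (assumed inputs).** Take n = 50 and m DFS events. Of these, t are scan-prompted and drawn from the 10 highest metric values; the other m − t fall at random among the remaining men. The metric has no true value.

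The top 10 ranks average 45.5 and all ranks average 25.5, so each prompted event adds 20 to the rank sum. The other m − t events come from men whose mean rank has dropped by 20t/(50 − t). The net excess is 20t − (m − t) × 20t/(50 − t) = 20t(50 − m)/(50 − t). Dividing by m(50 − m):

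expected AUC = 0.5 + 20t / [m(50 − t)]

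For m = 8, t = 2: 0.5 + 40/(8 × 48) = 0.604. The last column is the share of 20,000 simulated trials in which a two-sided 5% test of the linear-regression slope rejects.

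| Events m | Prompted t (share) | AUC | Rejections |
|---|---|---|---|
| 8 | 2 (25%) | 0.60 | 13% |
| 8 | 3 (38%) | 0.66 | 27% |
| 8 | 4 (50%) | 0.72 | 50% |
| 10 | 2 (20%) | 0.58 | 11% |
| 10 | 3 (30%) | 0.63 | 20% |
| 10 | 5 (50%) | 0.72 | 62% |
| 12 | 3 (25%) | 0.61 | 17% |
| 12 | 4 (33%) | 0.64 | 31% |
| 12 | 6 (50%) | 0.73 | 72% |

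With t = 0 the AUC is 0.50 and about 5% of trials reject. Rounded to shares of 25%, 33% and 50%, the AUC is about 0.60, 0.65 and 0.72.

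A stricter rule, in which the men with the very worst scans get the event on top of an assumed 10% to 25% rate of unrelated failure, gives an AUC of 0.54 to 0.60 for one prompted event, 0.58 to 0.66 for two and 0.61 to 0.71 for three.

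**The case against.** The strongest reply is that this argues from silence in a condensed article. Masking of reads, the definition of clinical metastases and event review may well be settled in the full protocol. No sentence says that 6- or 24-month results will be acted on. The rule that takes men off protocol concerns the baseline scan only, and the remark about earlier salvage is background. This stands as a limit. A reader might infer that the scans will drive DFS events, or that the analysis correlates the scan with itself; the article supports neither. It does commit to a predictor and an outcome that can overlap, and it states no safeguard.

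The direction is also open. The responses to recurrence that the article discusses include local salvage and metastasis-directed therapy. Neither is a DFS event, and either could delay biochemical failure and weaken the correlation. This stands, so a claim that the result would certainly be inflated goes too far.

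The illustration is severe. Every prompted event comes from the top fifth of the same metric, the metric has no true value, and a man who would have failed within 5 years anyway is a proper event however he was found. The background reports biochemical failure at 5 years in 57% of men with a positive 2-year biopsy, so many scan-found recurrences could be real. AUC is also not the measure of the linear regression, which is why the table adds slope-test rejections. These points make the figures an upper end and not an estimate.

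Finally, the article already plans to correlate imaging with the 24-month biopsy and with PSA, neither of which needs a clinician to act on the scan. That gives partial protection, but not for the DFS claim itself.

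**Conclusion.** The concern holds in a limited form. As stated in the article, the imaging-DFS correlation is open to incorporation bias through two of the four DFS components. Biochemical failure and death do not depend on how the scan is read.

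The actual size cannot be computed, because neither the number of DFS events nor the number prompted by scans is given. Under the assumptions above, the apparent AUC for a worthless metric could reach about 0.60 to 0.72. The useful message is sensitivity: with perhaps 8 to 12 events, two or three scan-prompted ones are enough to matter. Upward bias is more likely than downward but is not established. The full protocol may already answer part of this.

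**What to change.** Record prospectively, for each DFS event, what prompted it: a PSA rise, symptoms, a study scan, other imaging or another cause.

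For the imaging-DFS analyses only, prespecify a sensitivity analysis that counts biochemical failure, death, and metastases or salvage ADT whose recorded prompt was something other than a study scan. Report it beside the main analysis and interpret the biomarker claim in light of both. The two need not agree: with so few events, a difference may be no more than low precision.

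The cost is one data field and one extra analysis. The sensitivity analysis will have fewer events and will leave out some true failures that imaging found first, which is why it should accompany the main analysis and not replace it. The clinical DFS estimate and patient management are unchanged.

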We plan to evaluate the safety of SBRT with PSMA PET/MRI-guided focal boost in a prospective early phase trial, “PSMA MRI Guided prOstate SBRT(ARGOS).” As noted, while the advanced imaging techniques described show promise for the characterization of primary or recurrent prostate cancer, no study has prospectively and longitudinally evaluated them after primary radiotherapy to characterize expected changes in response to treatment and to non-invasively identify early treatment failure. All patients in ARGOS will enter the translational component of the study Comprehensive, Longitudinal Evaluation of Imaging Biomarkers Post Radiotherapy (CLIMBER). We will use advanced imaging analysis techniques to evaluate longitudinal changes in a comprehensive battery of anatomic and functional prostate imaging panels using ^18^F-PSMA 1007 and mpMRI acquired prior to and after SBRT. ^18^F-PSMA-1007 is chosen given its favorable pharmacokinetics profile with primarily gastrointestinal elimination, reducing tracer accumulation in the bladder and allowing better visualization of prostate and pelvic lymph nodes. The knowledge obtained from ARGOS/CLIMBER will improve the understanding of imaging changes post-prostate SBRT and will have increasing clinical importance with increasing use of these techniques. The ARGOS/CLIMBER protocol as outlined below is due to open in early 2022, with a plan for accrual of 50 men over 3 years and with follow-up of up to 5 years for clinical endpoints.

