### Primary Endpoint and Sample Size

This will be a single-phase pilot study of 50 patients with a primary endpoint of GI and GU toxicity as measured by CTCAE v5.0.

Unacceptable toxicity will be defined as acute (6 weeks) or intermediate (6 months) grade >3 GI or GU toxicity. The proposed treatment will be deemed too toxic if >30% of patients have unacceptable toxicity. This study tests the hypothesis that acute toxicity is <30% (alpha = 0.05, power = 81%, one-sided, H0: p = .30, HA: p <.30), with an assumed true proportion in this study of 15%. These calculations were done based on a Z test (normal approximation). We will test this assumption with the exact test approach if we do not meet our target accrual of 50 men or the proportion of Grade 3 toxicity is significantly less than 15% (conditions where normal approximation is not met).

Given that the proPSMA study demonstrated that 16% of men with high-risk prostate cancer had extra-prostatic disease beyond regional nodal metastases at initial staging and the fact our population will be a mix of high-intermediate and high-risk men, we will plan to enroll a total of 55 men (22). Those men with extra-prostatic spread beyond regional pelvic lymph nodes on their pretreatment PSMA PET imaging will be treated off protocol at the attending physician’s discretion.

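### Imaging changes are related to 5-year DFS by linear regression, which cannot handle men censored before 5 years; the harm depends on a DFS coding the plan does not state

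*Protocol article*

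**What the plan says.** Under Translational Imaging Endpoints, the article states: "We will correlate changes in PET and mpMRI metrics at 6 and 24 months with 5-year DFS using linear regression models". It does not say whether the DFS variable is time to event, event status at 5 years, or something else, or which side of the regression it is on.

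Under Disease-Free Survival, the endpoint is an event composite: "Five-year DFS will be determined as a composite of biochemical control, patient death or development of clinical metastases, or institution of salvage ADT". It is analysed as such: "DFS will be estimated with a Kaplan–Meier (KM) curve, with the 5-year estimate extracted from the KM curve".

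On follow-up, the Introduction and Background closes "with a plan for accrual of 50 men over 3 years and with follow-up of up to 5 years for clinical endpoints". Table 4 (Study Design) schedules visits at 6, 12, 18 and 24 months and then every 6 months from 30 to 60 months. The article names no censoring-aware model for the imaging analysis and gives no rule for men followed for less than 5 years.

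**The concern.** The two sections treat one endpoint in incompatible ways. A Kaplan–Meier 5-year estimate belongs to the group and cannot serve as a man's outcome in a regression. A value per man must therefore come from elsewhere, and each candidate has a defect:

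- **Observed time.** A man lost at 3 years is treated as if he had failed at 3 years. Even with no loss, all event-free men pile up at 60 months.
- **Status at 5 years.** A man lost event-free at 3 years has no value. He is either dropped or scored as disease-free.
- **Imaging change as the dependent variable.** The DFS status on the other side is still missing for the same men.

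Timing adds a problem. A 24-month change exists only for men still followed and imaged at 24 months. Counting DFS from treatment mixes in time, and possibly events, from before the marker was known.

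At stake is the credibility of the imaging biomarkers for 5-year DFS, a stated aim of the translational component. With few events, lost information is costly, and a spurious biomarker is easy to find if follow-up depends on the scan.

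**Working it through.** **The plan's own figure.** No power is given for this analysis. The only power figure is 81% for the toxicity test (Primary Endpoint and Sample Size). It reproduces: Φ[((0.30 − 0.15)√50 − 1.645√(0.30 × 0.70)) / √(0.15 × 0.85)] = Φ[(1.061 − 0.754) / 0.357] = Φ(0.86) = 80.5%. It says nothing about the DFS regression.

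**Inputs.** From the article: 50 men and a 60-month horizon. Assumed, because the article gives none of them: 5-year DFS of 75% or 85%, exponential event times, a standard normal marker, hazard ratio 2 per SD when there is an effect, and 20% or 40% of men censored early. Tests are two-sided at 5%.

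**Methods compared.** (a) Linear regression on 5-year status, censored men dropped; (b) the same, censored men coded event-free; (c) linear regression on observed time; (d) Cox.

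**Loss at a constant rate over 5 years, unrelated to the marker: power** (3,000 simulated trials per row)

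| 5-year DFS | Loss | (a) | (b) | (c) | (d) |
|---|---|---|---|---|---|
| 75% | none | 69% | 69% | 61% | 71% |
| 75% | 20% | 62% | 63% | 38% | 65% |
| 75% | 40% | 53% | 54% | 25% | 58% |
| 85% | 20% | 46% | 47% | 23% | 47% |
| 85% | 40% | 38% | 39% | 13% | 41% |

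At 20% loss, before rounding, (c) trails Cox by 64.5 − 38.3 = 26.2 points (DFS 75%) and 47.0 − 22.9 = 24.1 points (DFS 85%). Method (a) trails by 64.5 − 61.9 = 2.6 and 47.0 − 45.5 = 1.5 points. About 41 of 50 men then have known 5-year status, and about 7 to 13 events are observed.

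**20% of men censored uniformly between 24 and 60 months: power.** Repeated runs gave, for (c) against Cox, 41% vs 60% and 44% vs 62% at DFS 75%, and 25% vs 42% and 26% vs 44% at DFS 85%. The gaps are 17 to 19 points. For status, one run gave 59% (a) and 60% (b) against 61% for Cox at DFS 75%, and 41% and 43% against 41% at DFS 85%. Across all runs, status lost at most about 4 points.

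**False positives, no true effect**

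| Censoring | (a) | (b) | (c) | (d) |
|---|---|---|---|---|
| Unrelated to marker | 4–7% | 4–7% | 4–7% | 4–7% |
| Constant-rate loss, 20%, loss HR 2 per SD | 6% | 5–6% | 27–33% | 5% |
| Constant-rate loss, 40%, loss HR 2 per SD | 8% | 6–8% | 56–66% | 5–6% |
| Uniform 24–60 months, 20%, log-odds ±1 per SD | 6–9% | 5–6% | 14–28% | 3–5% |

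Under the uniform pattern with 40% censored, (a) reaches 10–13%.

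**Limit of the simulations.** The marker was placed at time zero with 60 months to follow. A landmark at 6 or 24 months leaves fewer events, so absolute power would be lower. The comparison between methods is what carries over.

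**The case against.** The case for leaving this alone is substantial in parts.

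- **Status at 5 years is the more natural reading** of a 5-year DFS outcome, and the next step in that section is classification. On that reading the power loss is small. This stands, and it limits the size of the point. It does not settle which coding is meant, and it leaves men with incomplete follow-up without a proper value.
- **Censoring may be light.** Table 4 takes every man to 60 months, so "with follow-up of up to 5 years for clinical endpoints" may state a per-patient maximum, and death is itself a DFS event. This stands as a caution: the 20% and 40% are assumptions. But the article does not assure complete 5-year status. In Table 4 as extracted, PSA is marked to 24 months but not for the 30–60 month visits, although biochemical failure is a DFS component.
- **Scan-dependent follow-up is not documented.** The visit schedule is the same for everyone. A reader might infer that the method will generate false biomarkers. The documents do not support that, because inflation arises only if censoring is related to the marker, and it is large only for regression on observed time.
- **The classifiers.** A reader might infer that "We will develop radiomics-based classifiers to predict 5-year DFS" carries the same error. The article does not state how that outcome is coded, and a condensed article may leave it to the full plan. It is no finding here.
- **Fitted probabilities below zero** do not by themselves invalidate a test of association, and the reported 5-year DFS estimate is safe because it comes from Kaplan–Meier.

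**Conclusion.** The point holds in limited form. Linear regression is a stated method that does not fit the endpoint as the article itself defines and estimates it, and nothing else in the article repairs this.

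The cost is conditional. At 20% censored, regression on observed time loses about 17 to 26 power points against Cox, and its false-positive rate is about 14–33% if censoring follows the scan, otherwise near 5%. Regression on 5-year status loses at most about 4 points. Its false positives reach about 13% only with 40% marker-related censoring and censored men dropped. All of this rests on the assumed DFS rate, effect size and censoring, none of which the article gives. If every man were followed to an event or to 60 months, the status reading would leave only a straight-line model for a yes/no outcome.

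This is a secondary, translational analysis in a pilot ("This will be a single-phase pilot study of 50 patients") with a toxicity primary endpoint, and no sample size or stopping rule depends on it. It should be fixed before the DFS analysis but does not threaten the trial.

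**What to change.** For the DFS association only, replace linear regression by Cox regression:

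- Use a penalised fit (for example Firth) with few predictors, because few events are expected.
- Start the clock at a landmark, the 6-month or the 24-month scan according to which change is analysed.
- Restrict each analysis to men who are event-free and imaged at that landmark.
- Censor men without an event at their last DFS assessment, and report hazard ratios with confidence intervals.

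Keep linear regression and the linear mixed models for continuous outcomes such as SUV change.

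As a secondary suggestion, say how any classifier of 5-year DFS accounts for men censored before 60 months, for instance by censoring-weighted or time-dependent ROC at 60 months.

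The cost is a change of wording and standard software, with no extra data. The landmark gives up events that occur before the scan, which the change in imaging could not have predicted anyway.

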Identification of local recurrence after EBRT has been explored with timed biopsy or mpMRI after radiotherapy (38). Prostate biopsy at 2 years posttreatment has been associated with clinical endpoints such as subsequent BF and distant metastases (36, 39). However, drawbacks of biopsy include unreliable results at earlier timepoints and potential morbidity (39). “Metabolic clearance” as defined by serial MRI with spectroscopy has been associated with durable biochemical control in retrospective series of men treated with conventional external beam radiotherapy (40–43). Recently, standardized mpMRI reporting for the locally recurrent disease has been proposed but has not yet been validated in larger prospective series (44). Additionally, there is a lack of prospective studies validating posttreatment mpMRI as a predictive biomarker in larger populations and men treated with SBRT.

PSMA-targeted PET/CT in addition to mpMRI improves detection of local recurrence after EBRT (45). However, while criteria for the response have been broadly defined (46), the significance of PSMA response and correlation with clinical endpoints are not known (47). As such, longitudinal monitoring of PSMA PET/CT changes post-radiotherapy, including changes in SUVmax and other PSMA PET based metrics, should be investigated as potential non-invasive biomarkers of treatment response after SBRT to the prostate. Integration of earlier PET-based response assessment, compared to triggered restaging at the time of BF, may provide an opportunity for earlier targeted salvage, but a lack of prospective longitudinal series of men so monitored is a gap in the current evidence base (23). Indeed, reports of false-positive PET scans in previously treated patients underscore the importance of systematically characterizing the normal patterns of PSMA PET/CT changes after SBRT and their correlation with clinical endpoints (48, 49).

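### Relating imaging change to 5-year DFS without the baseline value can mislead: an absolute SUV change may largely restate baseline uptake, and percent change is not a sure remedy

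*Protocol article*

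**What the plan says.** Under Secondary Endpoints, Translational Imaging Endpoints, the protocol article names the predictor, the outcome and the model in one sentence: "We will correlate changes in PET and mpMRI metrics at 6 and 24 months with 5-year DFS", by linear regression. It does not say whether change is absolute, percent or a log ratio. It neither includes nor excludes the baseline value as a covariate.

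The same section describes related analyses:
- "Changes in SUV metrics (SUVmax, SUVmean) within PSMA PET regions of interest (ROI) will be compared" between the pre-treatment and 6-month scans, with waterfall plots.
- A linear mixed model "will be used to compare pretreatment vs. posttreatment SUV values at multiple timepoints".
- Response rates by a cited consensus guideline.
- Classifiers on pretreatment images, and a delta-radiomics analysis.

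The metrics go beyond uptake: "Quantitative MRI metrics will be extracted, including ADC and pharmacokinetics parameters derived from dynamic PET and DCE-MRI".

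The Introduction and Background says that "the significance of PSMA response and correlation with clinical endpoints are not known". Table 4 schedules PSMA PET/MRI before treatment and at 6 and 24 months.

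**The concern.** Follow-up minus baseline contains baseline with a negative sign. When treatment removes most of the uptake, the man with the highest starting SUV tends to show the largest fall, however well or badly he responded. If starting uptake also carries prognosis, the regression on change picks up that prognosis and presents it as a response effect, in the direction of larger fall, worse outcome. A true effect of residual uptake can be masked at the same time.

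The Study Design section says that serial imaging is meant to find biomarkers that predict 5-year DFS, and this regression is the most direct test of that. Because the article treats the link between PSMA response and outcome as unknown, a wrong-signed result could not be recognised as an artefact.

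**Working it through.** **The plan's own figures.** None bears on this analysis. The only power figure (81%, primary toxicity endpoint) recomputes to 80.5% by the stated Z test and is not in question.

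**Inputs from the article.** 50 men; predictor change; outcome 5-year DFS; linear regression. SUV means, SDs and the baseline-to-follow-up correlation are not given, so they are varied below.

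**Step 1: how much of absolute change is baseline.** Let k = SD(follow-up)/SD(baseline) and ρ be their correlation. Then

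corr(change, baseline) = (ρk − 1) / √(1 + k² − 2ρk).

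For k = 0.5 and ρ = 0.5: (0.25 − 1)/√(1 + 0.25 − 0.5) = −0.75/0.866 = −0.87, so R² = 0.75. For ρ from 0 to 0.9:

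| k | correlation | R² |
|---|---|---|
| 0.25 | −0.97 to −0.99 | 0.94–0.98 |
| 0.5 | −0.87 to −0.93 | 0.75–0.86 |
| 0.75 | −0.66 to −0.80 | 0.44–0.64 |
| 1 | −0.71 to −0.22 | 0.50–0.05 |

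Baseline dominates when follow-up spread is about half of baseline spread or less. It does not when the spreads are similar and correlated.

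**Step 2: percent change.** With log-normal SUV (log SD 0.4–0.7, median follow-up 20–50% of baseline), R² with baseline was 0.00–0.45 and the correlation ran from −0.67 to +0.58. The coupling is weaker but not absent.

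**Step 3: direction of the association.** Take failure risk = g·B + h·F + error, with standardised baseline B and follow-up F and error variance 1. The unadjusted correlation of change with failure is

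[g(ρk − 1) + h(k − ρ)] / √[(g² + h² + 2ghρ + 1)(1 + k² − 2ρk)].

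The partial correlation given baseline is h√(1 − ρ²)/√(h²(1 − ρ²) + 1). With ρ = 0.3:

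| g | h | k | unadjusted | given baseline |
|---|---|---|---|---|
| 0.5 | 0.5 | 0.5 | −0.26 | +0.43 |
| 0.5 | 0.5 | 1 | 0.00 | +0.43 |
| 0.5 | 0 | 0.5 | −0.39 | 0.00 |
| 0 | 0.5 | 0.5 | +0.09 | +0.43 |
| 0 | 0.5 | 1 | +0.26 | +0.43 |

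First row: [0.5(0.15 − 1) + 0.5(0.5 − 0.3)]/√(1.65 × 0.95) = −0.325/1.252 = −0.26. The rows show reversal, cancellation, a spurious association, dilution, and a case with the right sign.

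**Step 4: error rates with 50 men.** Assumptions: baseline SUVmax log-normal, median 12, log SD 0.5–0.7; residual fraction median 30%, log SD 0.4–0.6, independent of baseline; 5-year DFS 75%, so 50 × 0.25 = 12.5 expected events. At log SDs 0.6 and 0.5, ρk = 0.3·e^0.125 = 0.34 and k = 0.47. Step 1 then gives −0.66/0.738 = −0.89, as simulated. Share of trials significant at 5%; the first and last columns give the range over several runs, and the percent column is one run of 600 trials:

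| what truly matters (hazard ratio per SD) | absolute change alone | percent change alone | follow-up + baseline |
|---|---|---|---|
| baseline only (2) | 54–59% | 4.7% | 4.5–6% |
| baseline only (1.5) | 22–28% | 4.3% | 4–6% |
| residual fraction only (2) | 11–15% | 65% | 61–68% |
| both (2 and 2) | 20–25% | 56% | 59–70% |
| neither | 4–6% | not run | 5–6% |

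In the baseline-only rows, essentially every significant absolute change pointed to larger fall, worse outcome. In the both row, nearly every one had the wrong sign. Linear regression on the 5-year event and Cox regression gave the same pattern, so this point is separate from the choice of linear regression.

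**Step 5: non-proportional fall.** The percent-change column is good because Step 4 makes the fall strictly proportional. With an assumed background floor of residual uptake, percent change correlated about −0.75 with baseline. It was then significant in 34% of trials when only baseline mattered, against 6% with adjustment.

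**The case against.** The strongest reply is that the article does not commit to the harmful version. It never says that change is absolute or that the models exclude baseline, and a journal article often leaves covariates and derived-variable definitions to the full protocol or SAP. Under strictly proportional falls, unadjusted percent change does about as well as the adjusted model. Even absolute change is not mostly baseline when the two spreads are similar. Baseline images are also analysed in their own right, since the plan will "train support vector machines and random forest classifiers to predict response based on the pretreatment images". The analysis is exploratory, in a 50-man toxicity pilot.

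Much of this stands. A reader might infer that the planned predictor is baseline in disguise, that the models will certainly be unadjusted, or that aggressive high-uptake tumours will appear as large responders. The documents support none of these as fact. They give no SUV spreads, no prognostic effect of baseline uptake and no scale of change. Nor does a large fall from high uptake describe ADC.

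Three things remain. The article does name change as the predictor and linear regression as the model. Percent change is safe only if the fall is proportional, which nobody yet knows. The other planned analyses do not separate response from baseline: the mixed model does not involve DFS, the pretreatment classifiers use baseline alone, and no baseline adjustment is described for delta-radiomics.

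**Conclusion.** The point holds in conditional form. If change is an absolute SUV difference, uptake falls strongly after SBRT and baseline is not in the model, the predictor can be mostly baseline (R² 0.75 or more at a spread ratio of one half or below). If baseline uptake is also prognostic, the association with DFS can be falsely positive, diluted or reversed. Under the Step 4 assumptions, the chance of a spurious response finding is about 22–59%, against about 5% with baseline included. Dilution does not need a prognostic baseline: when only the residual fraction matters, detection drops from 61–68% to 11–15%.

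These sizes rest on assumed SUV distributions, hazard ratios and a 75% DFS, none of them in the article. The high-uptake mechanism is specific to PET uptake. For ADC and kinetic metrics only the general coupling of change and baseline applies, and no size was calculated for them. The primary endpoint, its power and the sample size are untouched. The change is worth making because the adjusted model does not depend on which scale of change is chosen.

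**What to change.** For each metric and time point, enter the follow-up value together with the baseline value of the same metric, using logs for SUV, and read the follow-up coefficient as the response effect. This is the same model as log ratio plus log baseline, because a·log F + c·log B = a·log(F/B) + (a + c)·log B, so the response coefficient a is unchanged. Apply the same structure to ADC and the kinetic parameters on a suitable scale, and state the scale of any change reported descriptively.

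The baseline scan is already scheduled for every man (Table 4), so the cost is a sentence of analysis text and one more parameter per model. With perhaps a dozen events (12.5 under the assumed 75% DFS), that parameter matters, and penalised estimation can handle it. No visit, scan or sample size changes.
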